## Abstract

**Method and design::**

In this pilot cross-sectional study, we will enroll 115 Chinese participants aged 30 to 75 years with ACS. Blood sample will be obtained after the first maintenance dose of aspirin and clopidogrel during morning time. Serum PCSK9 will be measured by an enzyme-linked immunoadsorbent assay. Platelet reactivity will be assessed by; Platelet activation (P-selectin and GPIIbIIIa expression using flow cytometry) and; Platelet aggregation using light transmission aggregometry in response to various stimuli. On-treatment platelet reactivity is measured by adenosine diphosphate-induced platelet aggregation. Binding of ox-LDL to platelet will be evaluated by flow cytometry. Spearman correlations will be used to determine association of serum PCSK9 with platelet functional parameters and platelet-ox-LDL binding. Additionally, continuous PCSK9 levels will be categorized into tertiles of equal size to investigate its association with on-treatment platelet reactivity.

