### 2.2. Study population and recruitment procedures

Patients aged 30 to 75 years presenting with ACS (unstable angina, ST-elevation or non-ST-elevation myocardial infarction) will be screened for eligibility. Voluntary patients will be enrolled after written informed consent is obtained. Immediately after the administration of loading dose of aspirin (300 mg) and clopidogrel (300 mg), blood sample will be harvested for further analysis of serum PCSK9, platelet reactivity and ox-LDL-platelet binding. To be more specifically, blood sampling will be performed before catheter procedures. Patients will be excluded with coronary stenosis < 50% as ascertained by coronary angiography. The inclusion and exclusion criteria are given in Table 1. The flowchart of the study is shown in Figure 1.

**Table 1 T1:** Inclusion and exclusion criteria.

Inclusion	Exclusion
• Patients aged 35–75 yr	• coronary stenosis < 50% as ascertained by angiography
• Presenting with ACS, including unstable angina, ST-elevation and non-ST-elevation myocardial infarction	• uncontrolled blood pressure, heart failure pulmonary dysfunction
	• severe hepatic, renal, hematologic, mental disorders, terminal illness (carcinoma, etc)
	• pregnancy or breastfeeding
	• reluctance to sign an informed consent form

ACS = acute coronary syndrome.

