#### 3.2.3. Platelet aggregation assay.

Platelet aggregation will be analyzed using light transmission aggregometry according to standard protocols.^[21,22,23]^ Sodium citrate anticoagulated whole blood will be handled within 1 hour. Samples will be centrifugated at 260g for 10 minutes to obtain platelet rich plasma (PRP) and additionally at 760g for 10 minutes to obtain platelet-poor plasma. Platelet concentration in PRP will be adjusted to 2 × 10^8^/mL by dilution with homologous platelet-poor plasma. After stimulation of ADP (10µmol/L) or (arachidonic acid, 0.5 mmol/L), adjusted PRP will be utilized for the assay and light transmission will be monitored by an aggregometer over 6 minutes. Aggregation is quantified with 100% aggregation corresponding to 100% light transmission and maximum platelet aggregation rate (MPAR) will be used for statistical analysis. ADP- and arachidonic acid -induced platelet aggregation will be recorded as MPAR_ADP_ and MPAR_AA_, respectively. In addition, we define high on treatment platelet reactivity (HTPR) as MPAR_ADP_ >59%.^[24]^

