#### 2.2.5. Statistical analysis.

Categorical variables will be reported as counts (percentage). Distribution of continuous variables will be assessed by the Kolmogorov-Smirnov test. Normally-distributed continuous variables will be expressed as mean ± SD. Non-normally distributed continuous variables will be expressed as median and interquartile range (IQR). Comparisons between the groups will be performed by Pearson chi-squared test, analysis of variance or Kruskal-Wallis test, as appropriate. The association of PCSK9 levels with platelet reactivity and ox-LDL-platelet binding will be evaluated by Spearman rank test. For further analysis, we will divide the cohort into tertiles of PCSK9 values. univariate and multivariate logistic regression will be used to analyze the association between PCSK9 levels with on-treatment platelet reactivity. All tests will be 2-sided with an alpha level of 0.05. Analysis will be performed using SPSS version 20.0 (SPSS Inc., Chicago, Illinois).

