## 3. Discussion

Patients who had a recent ACS remain at high risk of recurrent ischemic events despite the current evidence-based treatments, including dual antiplatelet therapy and lipid-lowering agents.^[28]^ Circulating levels of PCSK9 dynamically increase during ACS as a consequence of cardiac ischemia.^[29]^ A clinical study has revealed that PCSK9 inhibition may confer benefits during ACS through LDL-dependent mechanism.^[11]^ Intriguingly, beyond its effects on LDL metabolism, preliminary results suggest PCSK9 as a positive modulator of platelet activation in in vitro and in vivo models.^[15,30,31]^ On the basis of prior preclinical observations, we will demonstrate possible relationship between circulating PCSK9 and platelet reactivity using multiple platelet function assays in a Chinses ACS cohort. To the best of our knowledge, 1 study including Austrian ACS patients reported an association between increased serum PCSK9 levels and platelet aggregation in response to a single agonist ADP.^[27]^ It should be noted that a single measurement of platelet reactivity may lead to inaccurate evaluation of the in vivo status of circulating platelets.^[32]^ Here in our study, more detailed analysis of platelet reactivity will be undertaken by quantification of platelet activation markers and aggregation induced by various agonists.

In order to minimize confounding effects on platelet reactivity, several strengths in the methodology should be noted. For 1, to exclude any influence of antiplatelet drug effects on platelet status, only patients receiving dual antiplatelet therapy with aspirin and clopidogrel will be recruited. More specifically, blooding sampling will be taken immediately after the loading dose of aspirin (300 mg) and clopidogrel (300 mg) and before coronary angiography or percutaneous coronary intervention (PCI), because catheter procedure itself is traumatic to platelets and testing within 96 hours post-PCI seems highly unpredictable regarding ex vivo platelet reactivity.^[32,33]^ Further, experimental data revealed remarkable increase in PCSK levels at 12 to 96 hours after cardiac ischemia.^[34,35]^ In this regard, the optimal timing for testing platelet reactivity, along with its association with PCSK concentration should be prior to PCI procedures.

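### The single blood draw is given two incompatible times, and at one of them ADP-induced aggregation cannot be taken as on-treatment reactivity

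*Protocol article*

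**What the plan says.** **Time of the draw.** The Abstract (Method and design) says: "Blood sample will be obtained after the first maintenance dose of aspirin and clopidogrel during morning time". Section 2.2 says: "Immediately after the administration of loading dose of aspirin (300 mg) and clopidogrel (300 mg), blood sample will be harvested", and then that "blood sampling will be performed before catheter procedures". The Discussion agrees with Section 2.2: "blooding sampling will be taken immediately after the loading dose of aspirin (300 mg) and clopidogrel (300 mg) and before coronary angiography". It defends this time on two grounds: catheterisation disturbs platelets and makes testing unreliable for some days after PCI, and PCSK9 rises markedly between 12 and 96 hours from ischaemia.

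**Endpoint.** The Abstract says: "On-treatment platelet reactivity is measured by adenosine diphosphate-induced platelet aggregation". Section 2.3 (Platelet aggregation assay) says: "we define high on treatment platelet reactivity (HTPR) as MPAR_ADP_ >59" per cent. Section 2.5 (Statistical analysis) says: "univariate and multivariate logistic regression will be used to analyze the association between PCSK9 levels with on-treatment platelet reactivity". The Introduction motivates the study by platelet reactivity that persists in ACS patients despite aspirin and a P2Y12 antagonist.

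**The concern.** The sampling time fixes what each measurement means. With two times in the text, neither the person drawing blood nor the reader of the results can tell which drug state the platelet data describe, or at what stage after ischaemia PCSK9 was measured. By the protocol's own account, both the outcome and the exposure depend on this.

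Each time also carries its own problem. If Section 2.2 is followed, the outcome of the logistic regression carries an on-treatment label that the draw does not support, and the study cannot speak to residual reactivity under treatment. If the Abstract is followed, any patient catheterised between the loading and the first maintenance dose is sampled after the procedure, which the Discussion sets out to avoid.

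**Working it through.** No formula tests this point, so the statements are set side by side.

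| Place | Dosing point of the draw | Relation to catheterisation |
|---|---|---|
| Abstract, Method and design | First maintenance dose already given; morning | Not stated |
| Section 2.2 | Directly after the load of aspirin and clopidogrel | Before |
| Section 3, Discussion | Directly after the load | Before angiography or PCI |

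**Step 1: can one draw satisfy all three?** No. A sample taken directly after the load precedes every maintenance dose that follows it. A sample taken once the first maintenance dose has been given is no longer directly after the load. No section describes a second draw or links the two times.

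**Step 2: does the difference matter on the protocol's own terms?** Yes. The Discussion says that catheterisation alters platelets and that PCSK9 moves over the 12 to 96 hours following ischaemia. A later draw can therefore change both variables in the correlation.

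**Step 3: does the endpoint fit the Section 2.2 time?** Three statements have to be reconciled:

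- the draw follows the load directly, with no minimum interval;
- ADP-induced aggregation is named as on-treatment reactivity, and a maximum aggregation above 59% is classed as high on-treatment reactivity;
- logistic regression relates PCSK9 to on-treatment reactivity.

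Without an interval for the drug to act, nothing in the plan ensures that the sample reflects treatment. The value remains a valid aggregation measurement at that moment. The on-treatment label, the use of the cut-off under that label, and any conclusion about residual reactivity lack support.

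**Step 4: does the endpoint fit the Abstract time?** The label is then consistent with a draw taken after dosing has continued. The pre-procedure statement in Section 2.2 and the defence of it in the Discussion are no longer assured.

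**Reach.** Recruitment is 115. With the stated 20% attrition, 115 × (1 − 0.20) = 92 patients would remain evaluable. The timing conflict applies to all of them, because the draw supplies PCSK9, both aggregation measures, the flow-cytometry markers and ox-LDL binding. The labelling problem applies only to the analyses of on-treatment reactivity.

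**The case against.** The best case on the other side is that Section 2.2 and the Discussion agree almost word for word, the Discussion gives reasons, and the Abstract sentence stands alone without explanation. The simplest reading is a slip in the Abstract. That is plausible, but it does not close the point. The two statements still have to be reconciled, and the reading in favour of Section 2.2 is the one under which the on-treatment endpoint fits least well. Figure 1 might help, but it is not available here.

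It is also fair to say that the Spearman analyses remain interpretable at either time, provided a single time is used. That stands and limits the second half of the point to the on-treatment label and the analyses built on it.

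A reader might infer more than the document supports:

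- **That the endpoint is essentially pre-drug in nearly everyone.** The protocol gives no onset time for clopidogrel, and Table 1 does not exclude patients already taking it, so some could be on treatment at the draw. The supportable statement is that the endpoint cannot be taken to measure on-treatment reactivity.
- **That different sites will sample at different times, costing a calculable amount of power.** Section 2.1 describes one centre. A loss figure would need a share of samples at each time, a shift in reactivity between them and a true correlation, and the protocol gives none of these.
- **That the two times fall on different days.** The text does not say so; different dosing points are enough.
- **That the Discussion's aim "to exclude any influence of antiplatelet drug effects on platelet status" contradicts an on-treatment endpoint.** The sentence goes on to restrict recruitment to patients on aspirin plus clopidogrel. It can equally mean holding the regimen constant, which is compatible with an on-treatment endpoint.

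**Conclusion.** The point holds and should be corrected before the protocol is relied on. The text states two sampling times that one draw cannot meet. At the time given in Section 2.2 and the Discussion, the aggregation outcome cannot be taken as on-treatment reactivity, although the protocol defines and analyses it under that name. This is conflicting text, not detail left out of a condensed article.

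The contradiction follows from the wording and needs no outside fact. The endpoint conclusion rests on reading the word for directly after the load literally, with no interval implied. The consequence is one of meaning: which drug state and which stage after ischaemia the data describe. No bias, attenuation or loss of power can be quantified from the document, and none is claimed.

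**What to change.** 1. State one sampling time, in the same terms, in the Abstract, Section 2.2 and the Discussion. Which time is intended is for the sponsor to say.
2. Record the time from dose to sample for each patient, and the time from procedure to sample if the draw can follow a procedure.
3. Make the endpoint match. If the draw directly after the load is kept, describe the aggregation outcomes as reactivity at that time, and drop the on-treatment and HTPR label together with conclusions about residual reactivity under treatment. If the draw after the maintenance dose is kept, withdraw the pre-procedure statements in Section 2.2 and the Discussion.
4. Optionally, add dose-to-sample time as a covariate in the logistic model. This is useful only if that time varies between patients.

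The cost is a wording amendment and one or two time fields on the case report form. No extra patients or assays are needed.

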**Discussion::**

This study will reveal possible relationship between serum PCSK9 and platelet reactivity in the setting of ACS which may shed light on therapeutic potential in platelet inhibition by targeting PCSK9. The study will also explore the association of serum PCSK9 and platelet-ox-LDL binding, an important mechanism for platelet-LDL interplay, to provide mechanistic insight into PCSK9-mediated regulation of platelet reactivity.

## 1. Introduction

Platelet activation and aggregation play a central role in arterial thrombosis and in the pathophysiology of acute coronary syndrome (ACS).^[1]^ Whereas despite the use of aspirin and a P2Y_12_ antagonist, a standard antiplatelet regimen in ACS, recurrent thrombotic events still occur in some patients, which is related to insufficient inhibition of platelet reactivity.^[2,3]^ The mechanisms that underlie the residual platelet hyper-reactivity in ACS is multifaceted where the involvement of low-density lipoprotein (LDL) is crucial.^[4]^

Platelets are continuously exposed to circulating LDLs in the blood stream. Furthermore, platelets are also in close contact with oxidized LDL (ox-LDL) released from the ruptured plague in the setting of ACS.^[4]^ Mounting experimental evidence suggests that both native and ox-LDLs substantially affect platelet reactivity.^[5,6]^ By binding to scavenger receptors (SRs), LDLs and ox-LDLs alter platelet signal transduction cascades, resulting in platelet hyper-sensitivity to the activating stimuli.^[7]^ More importantly, binding of ox-LDL induces platelet activation followed by shape change and aggregation, ultimately contributing to thrombus formation after plague rupture.^[8]^ In keeping with the preclinical data, Stellos et al^[9]^ reported increased platelet-ox-LDL binding in patients with ACS versus stable coronary artery disease. Therefore, the lipoprotein-platelet interplay provides a basis for the concept that regulation of ox-LDL-mediated platelet hyper-reactivity may translate into novel antiplatelet strategy for ACS patients.

Proprotein convertase subtilisin/kexin type 9 (PCSK9) fosters the degradation of LDL receptors, suppresses LDL clearance and subsequently raises circulating LDL and ox-LDL levels.^[10]^ A clinical trials has demonstrated that PCSK9 inhibition efficiently reduces recurrent cardiovascular events in ACS patients,^[11]^ which is considered largely LDL-dependent. Indeed, preliminary data also indicates other atherogenic mechanisms mediated by PCSK9 that are independent from lipid metabolism, several of which may affect platelet reactivity and thrombogenesis.^[12]^ In PCSK9^-/-^ mice, plasma level of soluble P selectin, a platelet activation biomarker,^[13]^ was significantly lower than that in control mice.^[14]^ This finding was supported by another study showing reduced FeCl_3_ injury-induced carotid artery thrombosis and platelet P selectin expression in PCSK9^-/-^ mice versus control.^[15]^ Whereas mechanistical data regarding PCSK9-mediated regulation of platelet reactivity is so far limited.

ox-LDL binds to platelet via lectin-like oxidized low-density lipoprotein-1 (LOX-1), a class E SR,^[16]^ and this interplay contributes to ox-LDL-mediated platelet hyperactivity and facilitates inflammation-driven atherothrombosis.^[17]^ Interestingly, upregulation of PCSK9 potently stimulates LOX-1 expression and ox-LDL uptake in macrophages in an inflammatory milieu.^[18]^ The above-mentioned clues support a hypothesis that PCSK9 may also be involved in modulating ox-LDL-platelet interplay, which may be associated with PCSK9-mediated regulation of platelet reactivity. This cross-sectional study will demonstrate serum PCSK9 level and its relationship with platelet reactivity and platelet-ox-LDL binding in Chinese ACS patients to address these knowledge gaps. We present the protocol in accordance with the Standard Protocol Items: Recommendations for Interventional Trials reporting checklist.

## 2. Methods/ design of the study

### 2.1. Study design and setting

The pilot study is designed as a single center cross-sectional trial, which will be conducted at the Center of Chest Pain of Affiliated Hangzhou Chest Hospital, Zhejiang University School of Medicine (Zhejiang, China). Ethical approval has been granted by the Institutional Ethics Committee of Affiliated Hangzhou Chest Hospital. This study has been registered in the Chinese Clinical Trials Registry (registration number: ChiCTR2100052578 at http://www.chictr.org.cn/). This study will follow the Strengthening the Reporting of Observational Studies in Epidemiology guidelines. We present the protocol in accordance with the Standard Protocol Items: Recommendations for Interventional Trials reporting checklist.

### 2.2. Study population and recruitment procedures

Patients aged 30 to 75 years presenting with ACS (unstable angina, ST-elevation or non-ST-elevation myocardial infarction) will be screened for eligibility. Voluntary patients will be enrolled after written informed consent is obtained. Immediately after the administration of loading dose of aspirin (300 mg) and clopidogrel (300 mg), blood sample will be harvested for further analysis of serum PCSK9, platelet reactivity and ox-LDL-platelet binding. To be more specifically, blood sampling will be performed before catheter procedures. Patients will be excluded with coronary stenosis < 50% as ascertained by coronary angiography. The inclusion and exclusion criteria are given in Table 1. The flowchart of the study is shown in Figure 1.

**Table 1 T1:** Inclusion and exclusion criteria.

Inclusion	Exclusion
• Patients aged 35–75 yr	• coronary stenosis < 50% as ascertained by angiography
• Presenting with ACS, including unstable angina, ST-elevation and non-ST-elevation myocardial infarction	• uncontrolled blood pressure, heart failure pulmonary dysfunction
	• severe hepatic, renal, hematologic, mental disorders, terminal illness (carcinoma, etc)
	• pregnancy or breastfeeding
	• reluctance to sign an informed consent form

ACS = acute coronary syndrome.

**Figure 1. F1:**
[figure not shown]
Flowchart of the study.

### 2.3. Measurements

#### 1.2.3. Serum level of PCSK9.

The blood samples obtained from patients will be taken into tubes and stored at −4°C. The samples will be at 300 g for 10 minutes to obtain supernatant and then immediately stored at 80°C until use. Serum levels of PCSK9 will be measured by a commercial enzyme-linked centrifuged immunoadsorbent assay according to manufacturer’s instructions.

#### 2.2.3. Platelet activation biomarkers.

Platelet activation will be assessed by flow cytometry as previously described.^[19]^ Platelet-bound P selectin and GPIIb-IIIa activation, biomarkers of platelet activation, will be analyzed at rest or stimulated with adenosine diphosphate (ADP).^[20]^ Briefly, whole blood will be collected in evacuated vacuum tubes containing 3.2% trisodium citrate at room temperature. 5 µL of citrated blood will be diluted with 100 µL of phosphate-buffered solution with or without stimulation by ADP (35µmol/L). Anti-CD61 will serve as control antibody to identify platelets from the whole blood. Monoclonal antihuman antibodies will be used to measure expression of P selectin (anti-CD62p) and activated form of GPIIb-IIIa (anti-PAC-1). Unspecific binding will be excluded by relevant IgG control antibodies. After staining, the cells will be fixed with 0.25% polyformaldehyde and stored at 4°C until analysis. Specific monoclonal antibody binding will be determined as mean fluorescence intensity.

#### 3.2.3. Platelet aggregation assay.

Platelet aggregation will be analyzed using light transmission aggregometry according to standard protocols.^[21,22,23]^ Sodium citrate anticoagulated whole blood will be handled within 1 hour. Samples will be centrifugated at 260g for 10 minutes to obtain platelet rich plasma (PRP) and additionally at 760g for 10 minutes to obtain platelet-poor plasma. Platelet concentration in PRP will be adjusted to 2 × 10^8^/mL by dilution with homologous platelet-poor plasma. After stimulation of ADP (10µmol/L) or (arachidonic acid, 0.5 mmol/L), adjusted PRP will be utilized for the assay and light transmission will be monitored by an aggregometer over 6 minutes. Aggregation is quantified with 100% aggregation corresponding to 100% light transmission and maximum platelet aggregation rate (MPAR) will be used for statistical analysis. ADP- and arachidonic acid -induced platelet aggregation will be recorded as MPAR_ADP_ and MPAR_AA_, respectively. In addition, we define high on treatment platelet reactivity (HTPR) as MPAR_ADP_ >59%.^[24]^

#### 4.2.3. Binding of ox-LDL on circulating platelets.

Whole blood will be studied for platelet bound ox-LDL by flow cytometric as previously reported.^[9]^ In brief, 5 µL of sodium citrate anticoagulated blood will be suspended in100 µL of phosphate-buffered solution. Platelets in the whole blood will be identified with anti-CD61. Then samples will be incubated with a polyclonal antihuman antibody (anti-Cu^2+^-ox-LDL) to detect ox-LDL on the surface of platelets and unspecific binding will be excluded by a relevant IgG control antibody. After staining, the cells will be fixed with 0.25% polyformaldehyde and stored at 4°C until analysis with a flow cytometer.

